**Figure 1 F1:**
[figure not shown]
Trial design.

In addition, more general Health and Safety guidance for EHOs develops the use of instruments such as the Risk Control Indicator (RCI) [18]. This instrument is used to describe and summarise risk in specific areas of operation and we therefore used existing templates to develop RCI metrics for use in premises. The group responsible for this development stage included senior EHOs, researchers and experts in areas relating to the NTE and the licensed trade generally. This development stage further fed into the creation of an intervention website designed for premises staff and contained information relevant to harm minimisation and their duties in that respect. The website contained videos that were amenable to view on a range of platforms (including smartphones and computers), documentation, and template forms that could be used as a basis for, for example, health and safety checks. The overall theme of the site was to provide positive and accessible messages on the advantages of a safe premises.

## Methods/Design

### Trial aims

The primary aim of the AWLPI trial is to determine the effectiveness of the SMILE intervention to reduce police recorded violence in licensed premises. Secondary aims include:

1. To determine whether the impact of the intervention changes over a twelve month follow-up period

2. To identify the costs associated with SMILE and evaluate cost effectiveness

3. To assess whether the fidelity of SMILE is maintained across Local Authorities (LAs)

4. To consider the relationship between outcomes and intervention reach, dose and receipt

5. To develop a revised logic model of the intervention

6. To determine the optimal format of the risk-led PL intervention for delivery by EHOs

### Trial design

Figure 1 provides a summary of the trial, a randomised controlled trial with embedded process and economic evaluations of the intervention designed to reduce alcohol-related violence in licensed premises across Wales.

### Ethical considerations

The trial received ethical approval from Cardiff University Dental School Research Ethics Committee (reference: 12/08).

### Study population

The study population is comprised of licensed premises that are based within the 22 LAs in Wales. To be eligible, premises must either be a public house, night club, or hotel with a public bar that has had one or more violent incidents (including Section 18/20, Section 47, common assault, affray, assault of a police officer) recorded by police in the twelve month period between May 2011 to April 2012. Other premises that are licensed for the sale of alcohol such as cafes, restaurants and entertainment venues (e.g. sports facilities, concert halls) are excluded.

### Sample size

A previous exploratory trial [19] suggested an overall group size of 272 premises provided a power of 90% to detect a 10% reduction in the failure rate (a day in which one or more violent incidents occurred) at a significance level of 0.05. Attrition is not a factor in this trial as EHOs have a statutory authority to enter premises and therefore adjustments for withdrawals are not applicable. Temporary and permanent suspensions of premises licenses are valid outcomes as they represent a form of intervention and are therefore accounted for in the group size. A 12 month follow-up period was chosen as the earlier exploratory trial suggested this offered the most likely opportunity to detect a significant effect in a full trial and could control for annualised cyclical variation within premises. As premises may appear in the police 12 month violence data but may have ceased trading between detection and the start of the project the total initial sample size was adjusted to 600.

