### Closure and replacement premises

Information on premises closure in the intervention arm will be provided by the EHO’s during the intervention period. In the event of premises closure before the intervention phase begins, it will be replaced with a premises randomly selected from a list of any remaining premises in that LA, matched by strata. In the event that no replacement premises is available in that strata no replacement occurs. Replacement premises will also be included in a sensitivity analysis. Potential differential rates of pre**-**intervention closures due to differences in data collection methodology between arms will be examined and explored in sensitivity analyses. In both the intervention and control arms after the intervention period, closure will be determined by telephone by research team staff. Additional replacement premises will also be included in a sensitivity analysis. Premises in the intervention arm that did not cooperate with EHOs or could not be accessed by EHOs in the allotted intervention period will be included in ITT analyses.

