**data based on 837 licensed premises eligible for inclusion in the AWLPI trial, data obtained from police incident reports between May 2011 - April 2012).

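### The stated 90% power for a 10% reduction does not fit the trial's own incident table: at the tabulated rate, 600 premises give about 54% (two-sided), and less once premises differ in underlying rate

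*Protocol article*

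**What the plan says.** The Sample size section of the protocol article states that an exploratory trial "suggested an overall group size of 272 premises provided a power of 90% to detect a 10% reduction in the failure rate", "at a significance level of 0.05". It defines a failure as a day with at least one violent incident. It gives no event rate, no sidedness and no variance, and does not say whether 272 is the total or the size of each arm. The initial sample is then raised to 600, only to allow for premises that stopped trading before the start. Follow-up is 12 months.

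The Randomisation section makes those 600 premises the intention-to-treat population. Outcome measures and Statistical analysis name the Andersen-Gill model as primary, count several incidents in one session as one failure, and bring baseline failure into the primary analysis.

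Table 1 (Trial intervention) lists violent incidents by Local Authority, with a total of 2,236. Its footnote describes them as "data based on 837 licensed premises eligible for inclusion in the AWLPI trial", from police reports for May 2011 to April 2012. Under Study population, each eligible premises has at least one incident in that year.

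**The concern.** A 10% relative reduction is a small effect, and a recurrent-event comparison needs several thousand failures to detect it with 90% power. The article adopts a power figure obtained elsewhere. It also prints the incident count of the population to which the figure is applied, and that count is too low to support it.

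At stake is how the result is read. If the trial finds no significant difference, a reader who trusts 90% power for a 10% reduction may conclude that an effect of that size has been made unlikely. On the trial's own figures, a true 10% reduction would be missed about half the time or more.

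**Working it through.** **Inputs from the protocol article.** Significance level 0.05, power 90% and a 10% reduction, taken as a hazard ratio (HR) of 0.90 (Sample size). 600 randomised premises (Randomisation), of which 300 are to be audited (Table 1), so 1:1. 2,236 incidents in 837 premises over 12 months (Table 1; the 22 rows do sum to 2,236).

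**Assumptions.** Two-sided testing, with one-sided shown alongside. A control-arm follow-up rate equal to the Table 1 rate.

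**1. Failures needed.** D = 4(z_α + z_β)² / (ln HR)².
- Two-sided: 4(1.960 + 1.282)² / (0.10536)² = about 3,786
- One-sided: 4(1.645 + 1.282)² / (0.10536)² = about 3,086

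**2. The tabulated rate.** 2,236 / 837 = 2.67 incidents per premises-year. Several incidents in a session count as one failure, so this is an upper bound on baseline failure-days.

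**3. Expected failures and power.** Failures = premises × 2.671 × 0.95, where 0.95 averages a control arm at 1 and an intervention arm at 0.90. Power = Φ(0.10536 × √D / 2 − z_α).

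| Premises | Failures | Two-sided | One-sided |
|---|---|---|---|
| 272 in total | 690 | Φ(1.384 − 1.960) = 28% | 40% |
| 272 per arm (544) | 1,381 | Φ(1.957 − 1.960) = 50% | 62% |
| All 600 | 1,523 | Φ(2.056 − 1.960) = 54% | 66% |

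A Wald test on two Poisson rates gives 53.7% for 600 premises, two-sided.

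**4. The most favourable draw of 600.** The other 837 − 600 = 237 premises hold at least one incident each, so the 600 hold at most 2,236 − 237 = 1,999. With each on its own day, failures are 1,999 × 0.95 = 1,899. Power is Φ(2.296 − 1.960) = 63% two-sided, 74% one-sided.

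**5. The rate that 90% would require.** Control-arm failures per premises-year, two-sided:
- 600 premises: 3,786 / (600 × 0.95) = 6.6, about 2.5 times Table 1
- 544 premises: 7.3
- 272 premises: 14.7

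One-sided with 600 premises, the rate would be 5.4, still about twice the tabulated one.

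**6. Can 272 be reproduced?** Not from the stated inputs. A two-proportion calculation with a 10-percentage-point absolute drop comes near it (20% to 10% gives 266 per arm). That cannot be the stated outcome: 2.67 failures a year is about 2.67 / 365 = 0.7% of days, which leaves no room for a 10-point fall.

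**7. Variation between premises.** The article gives no measure of it, so it has to be assumed. A simulation of 1,500 trials of 600 premises, with the log baseline count as covariate and robust variance, gives power of 42%, 36% and 36% for squared coefficients of variation of 0.25, 0.5 and 1.

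**8. Detectable reduction with 600 premises, 90% power, two-sided.**
- No variation between premises: power is 92% at HR 0.84 and 88% at HR 0.85, so about 15-16%.
- With variation and baseline adjustment: simulated power of 42% and 36% implies standard errors of 0.10536 / (1.960 − 0.202) = 0.060 and 0.10536 / (1.960 − 0.358) = 0.066. Then 1 − exp(−3.242 × 0.060) = 18% and 1 − exp(−3.242 × 0.066) = 19%.

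**The case against.** The strongest defence is that 272 came from an exploratory trial whose event rate is not shown. It may have been correct for a sample with more incidents, and a condensed article need not print the formula. This stands as far as it goes: the document does not show that the exploratory calculation was wrong, or that it ignored differences between premises. But the article applies the figure to this trial, and the two printed figures do not agree.

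It is also fair that Table 1 describes the index year, whereas follow-up runs to April 2014. A higher follow-up rate would raise power. It would have to be about 2.5 times higher, while selecting premises for having had an incident, collapsing incidents to sessions, and closures all push the other way.

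Four stronger readings are tempting and are not supported:
- **That 54% is a ceiling.** It is a central figure, assuming two-sided testing, the average rate of the 837 and no variation between premises. Neither the sidedness nor how the 600 were drawn from the 837 is stated.
- **That the best case is 68%.** That places all 2,236 incidents in the 600, which the eligibility rule excludes.
- **That power may be as low as 19%, or the detectable reduction as large as 27%.** These follow from an unadjusted analysis with a squared coefficient of variation of 1. The protocol puts baseline failure in the primary analysis.
- **That the sample size wrongly dismisses non-delivery.** The sentence "Attrition is not a factor in this trial as EHOs have a statutory authority to enter premises" concerns withdrawal, and outcomes come from police records. Premises that "did not cooperate with EHOs or could not be accessed by EHOs in the allotted intervention period" stay in the intention-to-treat set and may dilute the effect, but the document gives no figure for this, so it is a secondary matter.

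**Conclusion.** The point stands. As written for this trial, 90% power for a 10% reduction is contradicted by Table 1 under either reading of 272, with all 600 premises, one-sided or two-sided, and even with incidents concentrated in the 600 as far as eligibility allows. For the planned two-sided, baseline-adjusted analysis of 600 premises, power for a 10% reduction is roughly 36-54%. The upper end assumes no variation between premises; the lower end rests on assumed variation.

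The result depends on a follow-up rate close to the tabulated one. The exact percentages would move with that rate, but the shortfall is too large for a modest change to remove. The finding concerns the stated power only; the analysis model, the analysis set and the randomisation are not affected.

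**What to change.** Replace the 90%/10% statement with power and a minimum detectable hazard ratio computed from the Table 1 rate for the planned baseline-adjusted analysis. State the sidedness, whether 272 is the total or per arm, the assumed follow-up rate and the assumed variation between premises. Wording along these lines would do: at the index-year incident rate and two-sided 0.05, 600 premises followed for 12 months give roughly 36-54% power for a 10% reduction in failures, and 90% power only for a reduction of about 15-19%, depending on variation between premises. Replace the index-year incident rate by the failure-day rate if it can be extracted from the police data.

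Add that a non-significant result will be interpreted by its confidence interval, not by the planned power.

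The cost is one rewritten paragraph and a less favourable stated figure. No more premises are needed, and the primary analysis does not change.

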### Recruitment

Licensed premises were identified by searching police incident data and identifying those premises in which violent incidents were detected in the period May 2011 to April 2012. Police data provides the best way of measuring violence in licensed premises as they are routinely available across the study area. Although a proportion of violent incidents are not reported to the police, these data remain the most detailed and accurate records of incidents at the premises level. Other data sources such as Emergency Department attendance data are not universally available. Police incident data are broadly consistent across the 22 LAs taking part in the trial. In order to access police data, data sharing agreements were prepared and signed between Cardiff University and all four police forces in Wales. The agreements cover the period from May 2011 to the end of the trial follow-up period (April 2014). Data containing all violence against the person incidents were encrypted and anonymised before being given to members of the research team for screening. Incidents inside and in the immediate vicinity of licensed premises were identified from the police data based on the inclusion and exclusion criteria listed above. Premises receive the intervention as part of usual practice and as such, premises do not consent to participate in the trial and so withdrawal and loss to follow-up from the intervention phase of the trial is not possible.

### Randomisation

Premises are stratified by LA, licensable hours (up to 11 pm, open beyond 11 pm), and number of violent incidents in the twelve month period between May 2011 to April 2012 and randomly allocated into control or intervention group. Optimal allocation was used to carry out the randomisation [20], which was carried out by an independent statistician within the South East Wales Trials Unit (SEWTU). The randomised sample of 600 licensed premises comprises the intention to treat (ITT) population.

### Closure and replacement premises

Information on premises closure in the intervention arm will be provided by the EHO’s during the intervention period. In the event of premises closure before the intervention phase begins, it will be replaced with a premises randomly selected from a list of any remaining premises in that LA, matched by strata. In the event that no replacement premises is available in that strata no replacement occurs. Replacement premises will also be included in a sensitivity analysis. Potential differential rates of pre**-**intervention closures due to differences in data collection methodology between arms will be examined and explored in sensitivity analyses. In both the intervention and control arms after the intervention period, closure will be determined by telephone by research team staff. Additional replacement premises will also be included in a sensitivity analysis. Premises in the intervention arm that did not cooperate with EHOs or could not be accessed by EHOs in the allotted intervention period will be included in ITT analyses.

### Trial intervention

The intervention is a premises-level risk-audit (described below) that is designed to identify those areas of operation that contribute to alcohol-related violence. After the risk-audit is complete, feedback and advice are given to the Designated Premises Supervisor (DPS) in order for improvements (where applicable) to be made to premises operation. The intervention is delivered by EHOs as they have a history of enforcement and partnership working and are trained to deliver interventions and advice to small and medium sized businesses. Furthermore, EHOs have available statutory powers that allow their entry to premises and they are able to enforce change in the interest of public health and safety.

In order to enhance intervention fidelity, EHOs who deliver the intervention attended one of three training workshops, where the rationale for the intervention, the use of the audit tool, related materials including a website designed to support change in premises and EHO training materials were explained. The intervention is conducted in all 22 LAs in Wales, UK, and details of premises to be audited and the number of premises to audit per LA (see Table 1 for details) were given to EHOs at the beginning of the intervention period. Details of premises randomised to the control arm of the trial are not disclosed to EHOs and these premises therefore receive usual treatment. The usual treatment that premises receive from EHOs relating to violence is minimal; EHOs do not usually visit LP’s following violent incidents as part of normal practice.

**Table 1 T1:** Demographic data for each Local Authority in Wales

**Local Authority (LA)**	**Population***	**Population density rate (no. per hectare)***	**Violent incidents****	**Audits to complete**
Blaenau Gwent	69,814	6.4	40	6
Bridgend	139,178	5.6	69	13
Caerphilly	178,806	6.4	116	19
Cardiff	346,090	24.7	239	39
Carmarthenshire	183,777	0.8	124	18
Ceredigion	75,922	0.4	37	7
Conwy	115,228	1	128	10
Denbighshire	93,734	1.1	135	9
Flintshire	152,506	3.5	99	16
Gwynedd	121,874	0.5	165	12
Isle of Anglesey	69,751	1	54	7
Merthyr Tydfil	58,802	5.3	18	5
Monmouthshire	91,323	1.1	57	8
Neath Port Talbot	139,812	3.2	48	12
Newport	145,736	7.6	175	15
Pembrokeshire	122,439	0.8	96	11
Powys	132,976	0.3	68	12
Rhondda Cynon Taf	234,410	5.5	78	25
Swansea	239,023	6.3	178	26
The Vale of Glamorgan	126,336	3.8	25	8
Torfaen	91,075	7.2	57	9
Wrexham	134,844	2.7	230	13
Total	3,063,456	4.33	2236	300

*figures from 2011 census.

**data based on 837 licensed premises eligible for inclusion in the AWLPI trial, data obtained from police incident reports between May 2011 - April 2012).

### Risk-audit

The intervention is a Risk Led Intervention (RLI) developed from literature documenting features of premises that contribute to harm [21-23]. These interventions involve an initial risk-audit followed by an action plan which is given to the DPS. If the action plan is adopted, risks that promote harm within the premises will have been addressed and a reduction in alcohol-related harm is expected. Action plans require premises to make changes to operating procedures (e.g. reducing capacity, changing how security staff are deployed, checking patrons’ age at the door), improve staff training, as well as covering aspects of the internal and external environment (such as improving surveillance).

The RLI is made up of three components: first, EHOs audit intervention premises to identify areas that might increase the risk of violence, with findings recorded on a risk-audit form (see list of Information recorded by EHO’s on the risk-audit form(s)). For each area of premises operation covered by the risk-audit, EHOs record as much information as possible before giving an RCI score which corresponds with the perceived level of risk. Second, EHOs then record what further action (if any) is required at the premises. If risks are identified EHOs could respond in one or more of the following ways: 1) advise premises to make changes, i.e. verbally or by informal letter; 2) formally require changes to be made, i.e. by serving an improvement notice; 3) refer premises to police and LA licensing officers (who are able to place conditions on premises licenses); 4) a prohibition notice could be served to close the premises without notice if risks present a clear and immediate danger to the public. EHOs will conduct a second audit in premises where further action is required to assess whether the required changes have been made (and enforce where appropriate). The second audit will focus only on areas of risk identified in the initial audit. Depending upon the severity of the risk identified in the initial audit, the second audit will take place either one month (for serious risks) or three months (less serious risks) later, consistent with EHO usual practice. Following the initial risk-audit, EHOs will encourage intervention premises DPS and bar staff to access web-based training and instructional materials designed to engage them in harm reduction practices.

Information recorded by EHOs on the risk-audit form(s)

Audit date*

Audit start and end times*

EHO information (name, contact information, salary)*

Premises information (e.g. number of staff, food served, live music, etc.)

Areas of premises operation to assess

– Record checks (e.g. safety policy, risk assessments)*

– Visibility and lighting*

– Health and safety observation and checks*

– Surveillance*

– Noise and communication*

– Risk planning*

– Door management*

– Managing people*

– Staff training*

– Incident reporting (to RIDDOR, http://www.hse.gov.uk/riddor/, archived at http://www.webcitation.org/6L31Hvs03)*

– Glassware policy*

Questions for servers to assess the extent that premises policy reaches frontline staff

EHOs confidence in premises management*

Action taken by EHO*

* Indicates areas covered in the follow-up audit, if applicable.

### Web-based training and instructional materials

The intervention website contains information about harm reduction practices in licensed premises and provides guidance documents that can be downloaded and used by premises staff. The website also contains training and educational films, as well as a due diligence quiz, that are designed to provide instruction on how premises staff can reduce excessive alcohol consumption and violence. The website is available in English and Welsh [24].

Training and educational films are designed to increase knowledge of policies and practices that prevent and reduce excessive alcohol consumption and violence. The training and educational films offer guidance in the following areas: premises environment, security, crowding and how to de-escalate fractious encounters between customers. Films were also distributed by EHOs on DVD to cover premises without reliable internet access.

The due-diligence quiz comprises twenty-five questions that assess understanding and knowledge gained through viewing training films. Members of premises staff answering ≥50% of questions correctly receive a certificate of achievement that can be displayed in premises.

Reference materials were also provided. These are downloadable guidance documents, document templates, and posters that collectively aim to help premises staff reduce alcohol-related violence in their premises.

Business cards are used to advertise the website address. The business cards are given to premises staff by EHOs after the initial audit and are available in English and Welsh.

